**Protocol for Research Study**  
**(WIRB Protocol Number 20171006)**

**“Using Virtual Reality (VR) Models for Preoperative Planning for RALP”**

**I. STUDY OBJECTIVES.** To assess improvement in patient outcomes when using 3D models

**II. TARGET OPERATION.** Robotic Assisted Laparoscopic Radical Prostatectomy (RALP)

**IV. STUDY DESIGN.**

- a. **Trial Design:** A multi-institution, randomized, single-blind clinical trial
  - b. **Participants and Exclusion Criteria:** Eligible subjects identified from the medical record will be those who are 1) scheduled to undergo RALP surgery, 2) willing to consent to the surgery being performed by one of the surgeons participating in the study, and 3) willing to be assigned by randomization to one of the two groups in the study. Exclusion criteria are 1) prior prostate surgery, ablation, radiation, or androgen deprivation therapy, 2) lack of 3 Tesla or 1.5 Tesla with endorectal coil preoperative MRI imaging, and 3) inability to give informed consent.
  - c. **Randomization:** Each case will be assigned to one of the two preparation methods by a randomization procedure that is stratified by surgeon. Each surgeon-specific randomization schedule will be prepared using permuted blocks of size 2; i.e., each 2-patient block will be some permutation of {VR-aided, Control}. Thus, each surgeon's cases will be randomized in a 1:1 ratio. Use of permuted blocks thus avoids any confounding of preparation method with temporal trends (e.g., trend due to a learning curve.)
- Sequentially numbered opaque sealed envelopes (SNOSEs) will be prepared for each individual surgeon. Each envelope will contain the treatment assignment for one case (intervention or control). There will be an equal number of envelopes containing intervention assignments and control assignments; the total number of envelopes provided to each surgeon will be determined based on the surgeon's historical/anticipated case volume. The treatment code will remain concealed inside the envelope until the moment the case is ready to be prepared.

- d. **Blinding:** Patients, personnel gathering data from the video review, and statistician will be blinded. Control and intervention groups identifiers will be known only to the research personnel opening the sealed envelope for random group assignment and extracting patient data from the electronic medical record.
- e. **Intervention:** For intervention cases, surgeons will be provided with a 3D model to view (a) prior to the operation in addition to the MRI and biopsy results and (b) during the operation in addition to the MRI. For control cases, surgeons will view only the MRI and biopsy results prior to the operation and during the operation itself.
- f. **3D Model Creation and Delivery:** MRI scans will be deidentified and sent in Digital Imaging and Communications in Medicine (DICOM) format to Ceevra, Inc., where a patient-specific 3D model for each intervention patient will be created. The Prostate Imaging-Reporting and Data System (PIRADS) score will be used to identify and label prostate lesions. In addition, the biopsy report, will be used to create a patient-specific pathology map that will be included in the model to assist the surgeon in understanding the location of biopsy-proven cancer within the prostate. Models will be delivered to a mobile application on the surgeon's smartphone (Ceevra Reveal) and viewed as described above. In addition, the surgeon may view the model picture-in-picture on the robotic console screen using a video cable connection between the surgeon's smartphone and the surgical robot.
- g. **Outcomes Measures and Covariates:** The primary outcome measure is oncologic outcomes after RALP. This outcome will be measured at three time points: immediately postoperative, short term, and a final assessment when oncologic and functional outcomes have reached a steady state. Oncologic outcomes will be measured as margin status (positive or negative), PSA (linear and detectable/undetectable) at the initial assessment (which in most cases is three months postoperatively but may occur any time between 3 and 6 months), and PSA ( $>0.1$ ) at the final assessment (to be collected after 18 months but no later than 24 months). Additionally, any use of androgen deprivation therapy or radiation therapy will be captured at 24 months as an adverse oncologic outcome.
- Secondary outcomes are the urinary and sexual function of the patient, measured at the same three time points as above. For urinary function, this is bladder neck sparing (yes or no), measured immediately postoperatively, and incontinence pads per day, measured at both 3-6 months and 18-24 months postoperatively. For sexual function, this is nerve sparing (none, left, right, or bilateral), measured immediately postoperatively, followed by SHIM score, measured at both 3-6 months and 18-24 months postoperatively.
- Demographic data, disease-specific, surgery-specific, and surgeon-specific covariates will be collected from the medical record as well, see Appendix A.
- h. **Sample Size:** Sample size was calculated using prior data, including previous trials using 3D models in robotic partial nephrectomy. Previously we noted an effect size of 0.44 regarding the difference of outcome measures between 3D

model-aided and control groups. To account for multiple endpoints, we raised the sample size by 15%. Using the above method and paired t-test, the sample size of 90 (45 per arm) provided 80% power to detect clinically significant differences in our primary outcome measures with  $\alpha=0.05$ .

- i. **Statistical analysis:** Initial analysis will compare baseline characteristics between cases performed with (intervention) or without (control) models involved in preoperative planning. A two-sample t-test will be employed to compare means between groups and Chi-Square test or Fisher's exact test to assess the association between categorical variables. For outcome measures, the appropriate test will be used as described above to compare groups. To mitigate type I error due to multiple comparisons, and if the randomization yields balanced cohorts, a Bonferroni correction may be utilized for the primary and secondary outcomes. If randomization yields groups with statistically or clinically significant differences, adjusted differences between groups will be studied using a linear mixed model to regress the endpoint variables on covariates listed above, or the logistic mixed model, as appropriate.

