## VI. RESEARCHERS AND RESPONSIBILITIES

- a. **Principal Investigator (PI):** One PI from each participating Site.
  - i. Overall Site point person for study.
  - ii. Coordinates support for study with other Site participants, including Research Coordinator and surgeon users.
  - iii. Primary interface with the Site's IRB.
- b. **Research Coordinator ("RC").** One RC from each participating site. A researcher, fellow, resident or student identified and recruited by the PI. Key activities:
  - i. Identify upcoming cases to be included in the study and assign cases to control group or intervention group using block randomization.
  - ii. Identify, collect and manage:
    1. The MRIs from which the models will be created
    2. Data regarding Control Cases ("**Control Case Data**") and intervention cases ("**Intervention Case Data**")
  - iii. Deidentify each source MRI using deidentifying software (or ensures that Radiology deidentifies the image prior to delivery to the RC); deliver the deidentified image to Ceevra along with a unique identifier.
  - iv. Coordinate with surgeon users to ensure that both the model and the underlying MRI are reviewed prior to intervention cases.
  - v. Assist with administration of the surgeon surveys

- 130           **c. Surgeon Users.** Estimated between one and eight surgeon users (inclusive of  
131           the PI) from each site. Key activities:
- 132               i. Oversee receipt of informed consents from their patients participating in  
133               the study.
  - 134               ii. Provide the mobile phone used for viewing the models
  - 135               iii. Before each intervention case, review the source MRI and then review  
136               the associated model for purposes of case planning.
  - 137               iv. Participate in surgeon surveys.
- 138       **VII. MODEL CREATION KEY PERSONNEL**
- 139           **a. [name], CEO.** Overall Ceevra point person for study.
  - 140           **b. [name], CTO.**
    - 141               i. Oversees the creation of the models from the MRIs.
    - 142               ii. Oversees Ceevra software application and infrastructure.
    - 143               iii. Primary point of contact for user technical support issues.
- 144       **VIII. DATA COLLECTION AND SECURITY PLAN**
- 145           **a. Protocol for Case Data.** Case data will be extracted from the site's EHR system,  
146           and the surveys. It will be tracked via two files:

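### Fixed blocks of two within each unblinded surgeon reveal every second assignment before the envelope is opened, so patient selection can bias the comparison

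*Combined protocol and SAP*

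**What the plan says.** Section IV.c stratifies randomization by surgeon and fixes the block size: "Each surgeon-specific randomization schedule will be prepared using permuted blocks of size 2", so that "each 2-patient block will be some permutation of {VR-aided, Control}". The stated purpose is to keep preparation method from being confounded with time trends such as a learning curve. Each surgeon has a separate numbered series: "Sequentially numbered opaque sealed envelopes (SNOSEs) will be prepared for each individual surgeon". On concealment the section says: "The treatment code will remain concealed inside the envelope until the moment the case is ready to be prepared".

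Section IV.d lists who is masked: "Patients, personnel gathering data from the video review, and statistician will be blinded". Surgeons are not on that list. The same section says that only certain research personnel know the group identifiers, but this cannot be true of the operating surgeon, because section IV.e says: "For intervention cases, surgeons will be provided with a 3D model to view". Section VIII.b adds that the surgeon is notified when a model is ready.

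Section VI.b gives the research coordinator both tasks: "Identify upcoming cases to be included in the study and assign cases to control group or intervention group using block randomization". Section VI.c has the surgeons oversee consent. The documents mention no varied or withheld block size and no central assignment.

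**The concern.** Concealment means that whoever influences a patient's entry cannot know the arm that patient would receive. An opaque envelope achieves this only if its content cannot be deduced. Here it can be deduced for the second case of every block. The block size is printed in the protocol, the series belongs to one surgeon, the envelopes are numbered, and that surgeon and the coordinator know what the previous case received.

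A surgeon who expects the next case to be a control, or a model case, could offer, defer or not mention the study according to how difficult the case looks. The outcomes are sensitive to this. Margin status and later PSA depend on disease features visible before surgery, and nerve sparing and bladder neck sparing are the surgeon's own decisions. A systematic difference in case difficulty between arms would appear as an effect of the model.

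**Working it through.** The plan gives no figure for predictability, so there is none to reproduce.

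**Inputs from the documents:** block size 2, one case of each arm per block, one series per surgeon (IV.c); 90 patients, 45 per arm, alpha 0.05, effect size 0.44 (IV.h); one to eight surgeons per site, number of sites not given (VI.c).

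**Assumptions:** 15 patients per surgeon where a list length is needed; a two-sided test; steering of size *g*, in SD of prognosis.

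**1. Share known with certainty, blocks of 2.** The second slot of every block is determined by the first: 1/2 = 50%. In a 15-patient list there are 7 second slots: 7/15 = 46.7%. Over the whole trial the number is (90 − number of surgeons with an odd case count)/2. That is 45 if there are none, (90 − 8)/2 = 41 with eight, and (90 − 16)/2 = 37 with sixteen.

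**2. Best-guess accuracy, blocks of 2.** First slots are guessed correctly half the time and second slots always: (0.5 + 1)/2 = 75%. In a 15-patient list: (8 × 0.5 + 7 × 1)/15 = 11/15 = 73.3%. Simple randomization gives 50%.

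**3. Alternatives.** These come from exact enumeration of a 15-patient list. The guesser knows the possible sizes and that they are equally likely, but not the size in use, and updates after each assignment.

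| Block sizes | Known with certainty | Best guess correct |
|---|---|---|
| 2 (plan) | 46.7% | 73.3% |
| 4, fixed | 28.9% | 68.9% |
| 4 and 6, undisclosed | 5.9% | 67.6% |
| 2, 4 and 6, undisclosed | 3.5% | 68.6% |

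**4. Bias if only certain slots are steered.** Suppose patients in known model slots are better by *g* and those in known control slots worse by *g*. With half of each arm affected, bias = 0.5*g* − (−0.5*g*) = *g*. At *g* = 0.1 the bias is 0.1 SD, and 0.1/0.44 = 23% of the planned effect.

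**5. Effect on type I error.** With 45 per arm, SE = √(2/45) = 0.211 SD. With no true effect, the chance of a two-sided 5% rejection is 1 − [Φ(1.96 − bias/SE) − Φ(−1.96 − bias/SE)]:

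| *g* (assumed) | Bias (SD) | Type I error |
|---|---|---|
| 0.1 | 0.1 | 7.6% |
| 0.2 | 0.2 | 15.8% |
| 0.3 | 0.3 | 29.6% |

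**6. Bias if every slot is steered by best guess.** With accuracy *a*, each arm's mean shifts by *g*(2*a* − 1) in opposite directions, so bias = 2*g*(2*a* − 1). At *g* = 0.1 in a 15-patient list:
- Blocks of 2: 0.2 × (2 × 0.733 − 1) = 0.093 SD.
- Undisclosed 2, 4 and 6: 0.2 × (2 × 0.686 − 1) = 0.074 SD.

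The reduction is (0.093 − 0.074)/0.093, about 20%.

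**The case against.** The strongest counter-argument concerns size, not mechanism. The degree of steering is assumed. A bias of 0.1 SD needs every predictable slot, for every surgeon, to be steered in the same direction, and even then type I error rises only from 5% to 7.6%. Against someone who acts on best guesses, varied blocks cut the bias by only about a fifth. All of this stands, and it limits what can be claimed for the remedy.

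There are also partial safeguards. Candidates are identified from the medical record among patients already scheduled for surgery and must be willing to be randomized, which implies consent before the envelope is opened. But a deducible assignment is known before consent is sought, so the order of consent and opening does not help. Nor do the documents require consecutive enrolment. That a surgeon would influence who is approached is an inference from overseeing consent; it is plausible but not stated.

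Section IV.i plans covariate adjustment, and Appendix A lists preoperative PSA, Gleason score, PIRADS and risk category, among others. That would capture part of any selection. It is triggered only if the groups look different, however, and it cannot reach difficulty that was not recorded.

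Finally, blocks of 2 have a real purpose, and low-volume surgeons gain most from them. In an assumed 6-patient list they balance exactly, whereas varied blocks of 2, 4 and 6 leave about 15% of lists off by two. That cost is genuine but modest, and varied blocks still protect against time trends.

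**Conclusion.** The concern holds. As written, the second assignment of every block can be deduced by people who influence entry, and nothing in the documents prevents it. In complete blocks that is 50% of assignments, up to 45 of the 90 patients. The first case of each block remains concealed.

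Predictability follows from the design and rests only on the surgeon or coordinator keeping track of position in the block. The bias and type I error figures are illustrations: they depend on the assumed steering, on a standardized outcome scale and on 45 per arm. The documents do not show that selection will happen. It could not be reliably detected or fully corrected afterwards, so it should be dealt with before envelopes are issued.

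**What to change.** - **Block sizes.** Prepare each surgeon's envelopes with block sizes chosen at random from 2, 4 and 6. Have them generated by someone outside the sites, and leave the sizes out of the protocol the sites receive. Using only 4 and 6 is a reasonable alternative: slightly more assignments are certain (5.9% against 3.5%), but best-guess accuracy is slightly lower (67.6% against 68.6%).
- **Procedure.** Require signed consent and a logged eligibility record before the next envelope is opened. This documents the order of events; the block change is what reduces prediction.
- **Consistency.** Correct section IV.d so that it acknowledges that the surgeon knows the arm.

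The cost is new envelope lists and small text changes. The 1:1 ratio and protection against time trends are kept. A surgeon's list that stops partway through a block may end unbalanced by up to three cases.

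### The final PSA measure has no rule for men already given ADT or radiation, so tested alone it counts a treated, suppressed recurrence as not failing and dilutes a true difference

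*Combined protocol and SAP*

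**What the plan says.** Section IV.g states "The primary outcome measure is oncologic outcomes after RALP" and then lists several measures under that heading: margin status, PSA at 3-6 months (as a continuous value and as detectable or undetectable), and PSA above 0.1 "at the final assessment (to be collected after 18 months but no later than 24 months". A further sentence adds that "any use of androgen deprivation therapy or radiation therapy will be captured at 24 months as an adverse oncologic outcome".

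The section does not say whether final PSA and ADT/radiation form one endpoint, which takes precedence, or how PSA is read in a man already treated.

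Section IV.i does not settle it: "For outcome measures, the appropriate test will be used as described above to compare groups". Section IV.h refers to several endpoints and to primary outcome measures in the plural, and IV.i allows a Bonferroni correction. The covariates in Appendix A do not include postoperative ADT or radiation, so the adjusted models would not account for it either.

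On blinding, section IV.d says "Patients, personnel gathering data from the video review, and statistician will be blinded". Surgeons are not on that list, and under IV.e they view the model in intervention cases.

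**The concern.** ADT and radiation lower PSA. A man whose cancer recurs at, say, nine months and who is then treated may have a PSA of 0.1 or below at the 18-24 month reading. On the PSA measure taken alone he is indistinguishable from a man who never recurred. The measure then describes men who did not fail together with men who failed and were successfully treated, which is not the effect of the operation. The same man has opposite results on two items under one primary outcome.

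Two consequences follow. A true difference between arms is diluted. And if the share of recurrences treated before the reading differs by arm, the PSA comparison is biased in favour of the arm that treats more. In addition, because the plan leaves the combination open, the choice between PSA alone and PSA with treatment could be made after the results are seen.

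**Working it through.** **The plan's own figures.** The plan gives no recurrence rate, treatment rate or suppression rate, so it has no figure on this point to reproduce. Its sample size (45 per arm, section IV.h) rests on a standardised effect of 0.44, not on PSA failure rates. Only the 45 per arm is used here.

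**Inputs, all assumed except n**
- f = true failure rate by the final assessment: 25% control, 12.5% model
- r = share of failures given ADT or radiation before the final PSA
- s = share of those treated whose PSA is 0.1 or below at the reading: 60% to 80%
- n = 45 per arm (section IV.h)

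**Formula.** Observed rate of PSA above 0.1 = f × (1 − r × s). An endpoint that also counts ADT or radiation as failure returns f itself, if only men who fail are treated.

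**Step 1: same treatment share in both arms, r = 0.5**
- s = 0.6: control 0.25 × 0.70 = 17.5%, model 0.125 × 0.70 = 8.75%, difference 8.75 points
- s = 0.8: control 0.25 × 0.60 = 15.0%, model 0.125 × 0.60 = 7.5%, difference 7.5 points

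The true difference is 12.5 points. With equal r and s both rates are multiplied by the same factor, so the difference shrinks but cannot change sign in expectation.

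Power of a two-sided 0.05 comparison of proportions at 45 per arm (normal approximation) is about 33% for 25% vs 12.5%. It falls to about 23% for 17.5% vs 8.75% and about 20% for 15% vs 7.5%.

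**Step 2: more control failures treated, r = 0.7 control and 0.5 model**
- s = 0.6: 0.25 × 0.58 = 14.5% vs 0.125 × 0.70 = 8.75%, difference 5.75 points
- s = 0.8: 0.25 × 0.44 = 11.0% vs 0.125 × 0.60 = 7.5%, difference 3.5 points

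**Step 3: no true difference (25% in both arms), r = 0.6 control and 0.3 model**
- s = 0.6: 0.25 × 0.64 = 16.0% vs 0.25 × 0.82 = 20.5%, a spurious 4.5 points against the model arm
- s = 0.8: 0.25 × 0.52 = 13.0% vs 0.25 × 0.76 = 19.0%, a spurious 6 points

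**Step 4: what a reversal would take.** With 25% vs 12.5%, s = 0.8 and r = 0.3 in the model arm, the observed model rate is 0.125 × 0.76 = 9.5%. The control rate falls below that only if 0.25 × (1 − 0.8r) < 0.095, that is r > 0.775. About 78% of control failures would have to be treated against 30% in the model arm.

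**The case against.** A reader might infer that the plan scores treated men as successes and hides their failures. The documents do not support that. The sentence next to the PSA definition records any ADT or radiation as an adverse oncologic outcome under the same primary heading, so every such failure appears in the data. The plan never states that the PSA item is analysed without regard to treatment; it is silent. Even so, the ADT/radiation item is introduced as an addition, and section IV.h speaks of multiple endpoints. Item-by-item testing is therefore the natural reading, and on that reading the PSA comparison is affected.

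A reader might also infer that the comparison can reverse. Equal treatment shares only dilute it, the unequal case in Step 2 still favours the model arm, and Step 4 shows how large an imbalance a reversal needs. Nothing in the documents points to one. The documents do not say who decides on later ADT or radiation, or that knowing which planning aid was used would affect that decision. Bias from unequal treatment is therefore possible, not shown.

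The remedy also has a cost. If adjuvant treatment without PSA failure differs by arm, a composite takes in that difference. For illustration, take 25% PSA failure in both arms and treatment of 10% vs 5% of the remaining 75%. The rates become 25 + 7.5 = 32.5% vs 25 + 3.75 = 28.75%, a spurious 3.75 points. This stands, and it is the reason to report the components separately.

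Finally, only part of the primary outcome is affected. Margin status is untouched, and 3-6 month PSA mostly so.

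**Conclusion.** The point holds as a gap in the definition of one primary measure. The final PSA comparison has no rule for men treated before the reading and, tested alone, counts a treated and suppressed recurrence as not failing. On assumed rates of 25% vs 12.5%, with half of failures treated and 60-80% of those suppressed, a 12.5-point difference becomes 8.8-7.5 points, and power at 45 per arm falls from about 33% to 23-20%. Bias by arm would require unequal treatment shares, which the documents allow but do not show. The size depends wholly on assumed rates; the direction (dilution when treatment and suppression shares are equal) does not. This should be fixed before analysis, but it does not by itself invalidate the trial.

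**What to change.** - **Final assessment.** Define one oncologic-failure endpoint: PSA above 0.1 at the 18-24 month assessment, or any ADT or radiation started after surgery and by 24 months. Test it in place of the separate final-PSA and ADT/radiation comparisons, and report both components by arm.
- **Timing.** State that treatment is captured to 24 months for every man, including one whose PSA was read at 18 months, so that the two items cover a common period.
- **3-6 month assessment.** Count a man who has already started ADT or radiation as a failure in the detectable/undetectable analysis. State separately how he is handled in the continuous PSA analysis, where that rule gives no value.

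The cost is a change of definition. No new data are needed, and two tests become one. The downside is that adjuvant treatment without PSA failure counts as failure. This agrees with the plan's own labelling of such treatment as adverse, but any arm difference in its use enters the composite. The separate components let a reader see that. The change does not of itself yield a new sample size.

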**Appendix B**  
**Surgeon Pre- and Postoperative Survey**

Preoperative Survey (after viewing MRI but before viewing model)

- 1) Do you plan to perform nerve sparing (none, right, left, bilateral)
- 2) Do you plan to perform bladder neck preservation (yes, no)

Preoperative Survey (after viewing MRI and model)

- 1) Do you plan to perform nerve sparing (none, right, left, bilateral)
- 2) Do you plan to perform bladder neck preservation (yes, no)

Postoperative Survey

- 1) How would you rate your ability to see and define the area of cancer in the MRI (Likert)
- 2) How would you rate your ability to see and understand the relationship between the mass and the adjacent structures in the MRI (Likert)
- 3) How would you rate your ability to see and define the area of cancer in the model (Likert)
- 4) How would you rate your ability to see and understand the relationship between the mass and the adjacent structures in the model (Likert)
- 5) Were there any anatomical structures that you were able to see (or see better) in the model as opposed to the MRI (yes, no)
- 6) If answer to the question above is yes, please explain (free text)
- 7) Were there any structures or details that you could see in the source MRI that were either missing from, or appeared to be inaccurate in the model (yes, no)
- 8) If answer to the question above is yes, please explain (free text)
- 9) Did you modify your preoperative plan in any way as a result of what you saw in the model (yes, no)
- 10) If answer to the question above is yes, please describe how (free text)
- 11) Did you perform nerve sparing (yes, no)
- 12) How much did the model aid you in performing nerve sparing, if performed (Likert)
- 13) Did you perform bladder neck preservation (yes, no)
- 14) How much did the model aid you in performing nerve sparing, if performed (Likert)

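### Bladder neck sparing and nerve sparing record the unblinded surgeon's choice, but section IV.g counts them as the patient's urinary and sexual function at the immediate postoperative time point

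*Combined protocol and SAP*

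**What the plan says.** Section I gives the objective: "To assess improvement in patient outcomes when using 3D models". Section IV.g then sets out the secondary outcomes: "Secondary outcomes are the urinary and sexual function of the patient, measured at the same three time points as above".

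The measures named in section IV.g are:

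- Urinary, immediate: "For urinary function, this is bladder neck sparing (yes or no), measured immediately postoperatively".
- Urinary, later: "incontinence pads per day, measured at both 3-6 months and 18-24 months postoperatively".
- Sexual, immediate: "For sexual function, this is nerve sparing (none, left, right, or bilateral), measured immediately postoperatively".
- Sexual, later: "followed by SHIM score, measured at both 3-6 months and 18-24 months postoperatively".

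On blinding, section IV.d states: "Patients, personnel gathering data from the video review, and statistician will be blinded". The surgeon is not on that list, and section IV.e has the surgeon view the model both before and during intervention operations.

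Section V names a change in operative plan as one of the things the surgeon surveys assess. In Appendix B the surgeon is asked about intended nerve sparing and intended bladder neck preservation, once before and once after seeing the model. The postoperative survey then asks: "Did you modify your preoperative plan in any way as a result of what you saw in the model (yes, no".

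**The concern.** An outcome described as the function of the patient should describe the patient. Whether the bladder neck or the nerves were spared describes the operation. It may bear on later continence or erectile function, but it is not either of these, and section IV.g does not present it as a surrogate.

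The two items also lie on the path through which the model could act: the surgeon sees the model, may revise the plan, and operates accordingly. An arm difference in sparing is then evidence that surgeons behaved differently with the model. Under the label in section IV.g, the same difference would be reported as a change in urinary or sexual function, even if pads per day and SHIM did not differ between arms.

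Timing adds to the risk. Sparing is known at operation, whereas the final pads and SHIM results come at 18-24 months. Section IX provides for monthly meetings at which results to date are reported, so the sparing items would be the first secondary results available.

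**Working it through.** The plan gives no figure for this point, so there is nothing to reproduce. The check sets the sections side by side.

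**1. Count the secondary measurements (section IV.g).**

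| Domain | Immediate | 3-6 months | 18-24 months |
|---|---|---|---|
| Urinary | bladder neck sparing | pads per day | pads per day |
| Sexual | nerve sparing | SHIM | SHIM |

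Urinary 1 + 2 = 3; sexual 1 + 2 = 3; total 6. Operative steps: 1 + 1 = 2 of 6. Measures of the patient's function: 6 - 2 = 4 of 6, all at the two later time points. At the immediate time point no functional measure is listed in either domain.

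**2. Compare how the same items are treated elsewhere.** Section IV.g files sparing under function. Appendix B files it under the surgeon's intentions, asked before and after the model is viewed, with a follow-up on whether the model altered the plan. No section reconciles the two uses. The surgical technique list in Appendix A, where an operative step might be expected, does not include either item.

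**3. Ask whether blinding separates choice from measurement.** The surgeon makes the decision knowing the allocation. Section IV.d blinds the people who take data from video but does not say what they record. If they record sparing, that protects the recording. It does not blind the decision being recorded.

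**4. Ask what the planned test can show.** Section IV.i assigns the Chi-square or Fisher's exact test to categorical variables. Applied to yes/no, or to none/left/right/bilateral, such a test can show that the arms differ in the distribution of what was done. Neither section IV.g nor section IV.i orders the categories or says which result is favourable. The step from a difference in sparing to a difference in function therefore comes only from the label in section IV.g, not from the data or the test.

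**The case against.** The strongest reply is that the problem is narrow and visible. These are secondary outcomes. The text names them openly, so a careful reader can see what was measured. Pads per day and SHIM are prespecified at both later times, and section IV.g itself places the settled state of functional outcomes at the final assessment. This stands, and it sets the limit of the point: the objective can still be answered by the four functional measurements and the oncologic measures. It does not remove the mislabelling at the immediate time point.

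Several stronger readings are tempting, but the documents do not support them:

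- A reader might infer that the plan scores less sparing as worse function and more sparing as better. It assigns no score, order or direction. The absence of a direction is itself part of the point.
- A reader might infer that the protocol sets out to change sparing. It does not say so. The surveys show only that a change of plan was thought possible and worth recording.
- A reader might want to put a multiplicity cost on the two items. Section IV.i makes the Bonferroni correction optional, extends it over primary as well as secondary outcomes, and does not count the tests, so no particular threshold follows from the plan.
- A reader might infer that the relation between sparing and margin is lost, or that it can be recovered side by side. Both items are recorded for each patient, so a patient-level cross-tabulation is possible. But section IV.g records margin only as positive or negative. Whether a spared side had a positive margin cannot be read from the stated measures.

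**Conclusion.** The point holds for the immediate postoperative time point. Two of the six secondary measurements are operative steps chosen by an unblinded surgeon, and section IV.g counts them as patient function. A difference between arms on them would be a difference in surgical choice, and a report of it as changed urinary or sexual function would be wrong.

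The conclusion rests on the wording of sections IV.d, IV.e, IV.g and V and of Appendix B. It assumes that results will be reported under the labels in section IV.g. It does not depend on the sample size or on any significance threshold.

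The change is worth making because it is cheap and prevents a predictable misreading of the earliest secondary results.

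**What to change.** In section IV.g, reclassify bladder neck sparing and nerve sparing as operative process measures. Report them separately by arm as a description of how operations differed. State that conclusions about urinary and sexual function rest only on pads per day and SHIM at 3-6 and 18-24 months, and carry the same distinction into section IV.i.

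Optionally, add a descriptive patient-level table of nerve sparing (none, left, right, bilateral) by margin status (positive, negative) within each arm. This makes 4 × 2 = 8 cells for a planned 45 patients per arm, so it should not carry a test. Note beside it that margin side is not among the stated measures; a side-specific reading would need that information in addition.

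The main change is to wording and uses measures already planned. Its cost is that the trial makes no functional claim at the immediate time point.
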